## Abstract

**Introduction:**

Persistent pain after finishing breast cancer treatment is a common and disabling problem. The current state-of-the-art pain management advocates, in addition to biomedical (non-)pharmacological approaches, a biopsychosocial rehabilitation approach to address persistent pain, combining pain science education with promoting an active lifestyle through self-regulation techniques. We propose testing an innovative eHealth self-management support programme for this purpose in the breast cancer population with persistent pain after finishing cancer treatment. This delivery mode is believed to reduce barriers to pain self-management by providing timely, safe and cost-effective assistance addressing the biopsychosocial needs of patients. Utilising a chatbot format, the eHealth programme delivers pain science education and promotes physical activity (PA), personalised through decision-tree-based algorithms to support pain self-management. The programme aims to empower patients with understanding, coping skills and self-management techniques to reduce pain-related disability and enhance participation in daily life. The primary objective is to determine programme effectiveness compared with (1) usual care (superiority) and (2) a similar face-to-face pain self-management support programme (non-inferiority).

**Methods and analysis:**

A pragmatic, three-arm randomised controlled trial was started in April 2024 at the University Hospitals of Antwerp and Leuven and primary care settings in Belgium. Participants are breast cancer survivors with persistent pain after finishing cancer treatment. Two hundred seventy participants will be randomised to one of three trial arms: (1) eHealth self-management support programme, (2) usual care or (3) a face-to-face self-management support programme. The ‘eHealth self-management support programme’ begins with a pain science education (PSE) module to initially convey key pain-related concepts and provide personalised pain management tips. Then, the programme progresses to daily activity planning to promote an active lifestyle. Guided by the Health Action Process Approach (HAPA) model, participants set and review daily activity goals and track progress. The eHealth self-management programme uses a chatbot and is accessible on any digital device. The ‘usual care programme’ involves sending the participants a study-specific brochure by postal mail and does not include any formal PSE and/or PA programmes. They may pursue or continue self-initiated care. In Belgium, usual care primarily involves pharmacological treatment, general advice on PA and the provision of informational brochures. The ‘face-to-face self-management support programme’ mirrors the eHealth intervention, combining PSE with PA coaching. It starts with three individual sessions with a trained physical therapist for biopsychosocial assessment and PSE, followed by six sessions on goal setting and active lifestyle coaching. The educational content is delivered both verbally and in written form. The primary outcome will be pain-related disability 6 months after baseline assessment. As a key secondary outcome, the effect on pain beliefs and attitudes will be investigated after the educational part of the eHealth and face-to-face programme (ie, at 6 weeks after baseline). Other secondary outcomes related to other dimensions of pain and physical-, psychosocial- and health-economic outcomes will be assessed at 12 weeks and 6 and 12 months after baseline as well.

**Ethics and dissemination:**

The study will be conducted in accordance with the Declaration of Helsinki (2024). The protocol has been approved by the ethical committee of the University Hospitals of Leuven and Antwerp. Results will be disseminated via peer-reviewed scientific journals and presentations at congresses. Ethical Committee of the University Hospitals Leuven and Antwerp: BUN B3002023000132.

**Trial registration number:**

ClinicalTrials.gov Identifier: NCT06308029.

STRENGTHS AND LIMITATIONS OF THIS STUDYThis pragmatic trial includes broad eligibility (all ages, treatments, sexes/genders) and recruits from both primary care and hospitals, supporting strong external validity.Designed by an international, interdisciplinary team, the project is grounded in strong evidence and theory.A process evaluation is included to inform future scale-up decisions.External validity is limited by being conducted in a single country and requiring Dutch proficiency, potentially excluding some groups.The trial is powered (≥80%) for superiority and non-inferiority comparisons, but not necessarily for the combined endpoint.

## Introduction

 Breast cancer is the most prevalent cancer, accounting for over 33% of all cancers diagnosed globally.^1^ Advances in cancer screening and treatment have significantly increased survival rates, resulting in a growing population of breast cancer survivors. However, many survivors experience long-term, debilitating effects from the disease and its treatments, particularly persistent pain.^2^,^4^ A recent meta-analysis found that 45% of breast cancer survivors report persistent pain after completing primary treatments.^4^

Current cancer pain management predominantly relies on pharmacological approaches, including anti-neuropathic drugs which often have limited efficacy and some with significant side effects.^5^ Complete pain relief is rare with pharmacotherapy; most patients achieve only partial improvement, typically a 30%–50% reduction in pain intensity. In this, particularly opioids can be associated with significant side effects.^5^ Therefore, a more comprehensive approach to pain management is needed.

Chronic pain management in non-cancer populations has moved beyond medication-based approaches.^6^,^10^ Education, active and psychological therapies, and self-management skills are frontline interventions for persistent pain, as endorsed by the clinical guidelines.^6^,^10^ Modern Pain Science Education (PSE) aims to improve understanding of ‘how pain works’, including the biological basis of pain’s multifactorial character, the notion of variable sensitivity and the ‘over-protective’ nature of persistent pain.^11^,^13^ Also, contemporary PSE is grounded in educational and adult learning science principles, moving away from didactic teacher-centred methods or ‘information provision’ approaches.^14^ This approach empowers individuals by improving their understanding of pain, which can lead to better self-management and decision-making regarding their treatment. Meta-analyses have shown that PSE reduces pain, disability, pain catastrophising and kinesiophobia in adults with chronic musculoskeletal pain.^15 16^ For pain after cancer treatment, educational interventions show modest short-term effects on quality of life, particularly in global and emotional aspects, but not for pain in particular.^17^,^20^

Physical Activity (PA) is another crucial component in managing chronic non-cancer pain.^6^,^1021^ It can reduce pain sensitivity by its beneficial effects on the central nervous system, autonomic nervous system, immune system and musculoskeletal system.^22^,^25^ However, misconceptions about pain and PA often prevent individuals from adopting active lifestyles. PSE can prime patients for PA programmes by addressing barriers to behaviour change and bridging the intention-behaviour gap, enabling them to adopt an active lifestyle. This approach is effective in non-cancer populations.^1526^,^31^ Adopting an active lifestyle may require a behavioural change in which self-regulation techniques have proved useful.^32^ To our knowledge, no research has yet combined PSE with a PA behavioural intervention based on self-regulation techniques to support pain self-management in the cancer population.^33^

Implementing combined PSE and PA interventions presents challenges for patients and for the healthcare system. These challenges include the resource-intensive nature of face-to-face rehabilitation programmes, the burden of long-term medical follow-up, stress and inconvenience related to healthcare provider visits, and the need for personalised approaches tailored to individual patients' needs.^15 34 35^ Additionally, accessibility issues, such as mobility limitations and time constraints, limit the coverage of traditional face-to-face programmes. Integration of digital health interventions,^36^ including for pain management,^37^ is now being actively encouraged as a sustainable approach. eHealth interventions can deliver tailored information to large populations cost-effectively, offering widespread accessibility. eHealth self-management support programmes can support individuals to manage their symptoms, treatment and lifestyle changes. In their design, these programmes offer the opportunity to personalise information, advice and skills according to decision-making algorithms. Studies testing chatbot-based eHealth interventions in breast cancer populations and chronic pain settings report high patient engagement, satisfaction and usability, suggesting that chatbots can serve as effective, scalable tools for delivering personalised support outside traditional care settings.^38^,^40^ Evidence suggests that such programmes can positively impact both physical and psychological outcomes in chronic non-cancer pain.^3541^,^44^ However, little evidence is currently available for this approach to improve pain-related disability in the cancer population. A systematic review on effects of eHealth self-management interventions in the breast cancer population found only two uncontrolled studies that demonstrated significant decreases in pain intensity over time. Also, these studies did not involve eHealth interventions that offered tailorable content; their observed effects were not sustained over the long term.^35^

Given all this, the proposed project aims to evaluate the effectiveness of an automated and personalised eHealth self-management support programme for reducing pain-related disability in breast cancer survivors. This programme uses an innovative chatbot format to combine PSE with self-regulation techniques to promote PA after breast cancer, that is, the PECAN trial which stands for ‘Pain Education and Coaching of Activity Needs in breast cancer survivors’.

### Objectives

The primary objective of the study is to determine the effectiveness of an eHealth self-management support programme for persistent pain after breast cancer treatment on pain-related disability at 6 months after baseline, as compared with:

Usual care (ie, superiority of the eHealth self-management support programme).A self-management support programme delivered face-to-face in a physical therapy setting (ie, non-inferiority of the eHealth self-management support programme).

The secondary objectives of this study are to:

Determine the change in pain beliefs and attitudes at 6 weeks (ie, after the PSE component but before the PA component of the eHealth and face-to-face programme) (key secondary outcome).Examine if the eHealth self-management support programme has a relative benefit for other secondary biopsychosocial outcome parameters that have been aligned with the programme theory, encompassing pain-related, physical and psychosocial outcomes assessed at 12 weeks, 6 months and 12 months.Estimate its cost-effectiveness at 6 and 12 months.

Parallel to the effectiveness trial, a process evaluation will be performed to assess the implementation, the contextual determinants of implementation and the potential for scale-up.

## Methods and analysis

Described according to the Standard Protocol Items: Recommendations for Interventional Trials (SPIRIT) guidelines (http://www.spirit-statement.org/protocol-version/).

### Trial design and study setting

The trial is a parallel, three-arm pragmatic randomised study, approved by the Ethics Committees of the University Hospitals Leuven and Antwerp (BUN B3002023000132) on 30 January 2024. The first participant was enrolled on 26 May 2024. Recruitment is expected to continue until January 2028, resulting in the primary completion in June 2028. Given a 1-year follow-up, the anticipated study completion date is January 2029. A schedule of the trial is presented in table 1.

**Table 1 T1:** Schedule of enrolment, interventions and assessments of the PECAN trial

Timepoint	Study period							
	Enrolment		Allocation	Post-allocation				
	-t_2_ Referral	-t_1_ telephone consult	0	t_1_ baseline	t_2_ 6 weeks after baseline	t_3_ 12 weeks after baseline	t_4_ 6 Mo after baseline	t_5_ 12 Mo after baseline
Enrolment								
Eligibility screen	X							
Informed consent		X						
Randomisation			X					
Allocation			X					
Interventions								
				Education	PA coaching			
eHealth intervention			n=90	x	x			
Face-to-face intervention			n=90	x	x			
Usual care			n=90					
Assessments								
Pain-related disability (primary outcome)*				X		X	X†	X
Pain-related outcomes, including pain beliefs and attitudes (key secondary outcome)*				X	(X)†	X	X	X
Physical outcomes*				X		X	X	X
Psychosocial outcomes*				X		X	X	X
Health economic outcomes*							X	X

* See online supplemental appendix C for details on the content of the different assessments at each point in time.

† Primary endpoint of the trial.

† The key secondary outcome ‘pain beliefs and attitudes’ is the only outcome collected at 6 weeks.

PA, physical activity; PECAN, Pain Education and Coaching of Activity Needs in breast cancer survivors.

### Patient and public involvement in trial design

An advisory board with different interest holders, including Belgian and Flemish patient organisations (Kom Op Tegen Kanker, Stichting Tegen Kanker, ThinkPink and Envie), the Professional Association for physical therapists and general practitioners, and the National Institute for Health and Disability Insurance, was consulted during the initial grant preparation and trial setup. The feasibility, acceptability and utility of the eHealth approach was tested with consumers with lived or living experience of persistent pain after treatment for breast cancer, in collaboration with international partners within the authorship team.^45^

### Eligibility criteria

People with primary breast cancer who have undergone axillary surgery (axillary lymph node dissection or sentinel node biopsy, unilateral or bilateral) are eligible. Participants must be non-metastatic and have finished their primary treatment with curative intent at least 3 months before participating in the study. However, adjuvant hormonal therapy and immunotherapy are allowed. Additionally, participants must report to their healthcare provider persistent pain over the past 3 months that interferes with their daily activities. Given the pragmatic nature of this trial, self-report of persistent pain will be used as the definition for this eligibility criteria. Participants will be excluded from the study if they are unable to participate for the entire duration of the study, are mentally or physically unable to participate, do not have access to a digital device, do not speak/understand Dutch or have previously participated in a PSE programme.

### Participant screening, recruitment and consent

Participants experiencing persistent pain after breast cancer treatment are recruited in the University Hospitals of Leuven and Antwerp, as well as from general practitioners’ practices in Flanders and through self-referral. Following referral, an initial screening is conducted by a member of the research team. Eligible participants receive a detailed explanation of the study over the phone, along with an information sheet sent via email. Participants are not blind to the intervention nor the different arms. If needed, a second phone consultation is provided before obtaining informed consent. The consent form can be signed either digitally (via email) or on paper (via postal mail). An example of the informed consent form can be found in online supplemental appendix A.

### Allocation and randomisation

The randomisation process will be conducted using a Python script developed internally by a member of the research group, who is not involved in the recruitment, intervention, or analysis phases of the project. Participants will be randomised to one of the three treatment arms using the method of randomly permuted blocks with random block sizes (3–6). To maintain balance between intervention groups, randomisation will be stratified by recruitment setting (University Hospital Leuven/Antwerp University Hospital/general practitioners/self-referral). The script’s output will be transferred to a structured Excel file, which facilitates the allocation of each participant to their respective treatment arm while considering predefined strata (n=4) and assigns a unique study-specific identifier to each participant. Access to and utilisation of this Excel file will be restricted to the principal investigator and an independent member of the research group. This independent member is responsible only for allocating new participants to the treatment arms and assigning them study-specific identifiers, with no further involvement in the project.

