### Sample size

This study adopts a three-arm design to evaluate the eHealth intervention’s superiority to usual care and non-inferiority to face-to-face intervention using a hierarchical testing procedure.^63^ The trial will be termed successful if superiority of the eHealth intervention to usual care as well as non-inferiority of the eHealth intervention to the face-to-face intervention has been shown. A hierarchical testing procedure will be applied, first testing superiority, followed by testing non-inferiority if and only if superiority was shown. Consequently, no correction for multiple testing needs to be applied. Note that if superiority was shown, but showing non-inferiority failed, it is still allowed to conclude that eHealth intervention is effective, but not that it can replace the face-to-face intervention.

The primary outcome used to test superiority as well as non-inferiority is the PDI measured at 6 months. Both tests will be based on the comparison of the mean value after correction for the baseline PDI (Analysis of Covariance (ANCOVA) approach). The assumed SD of the PDI and the correlation between baseline and 6 months equal 15 and 0.65, respectively, and were obtained from pilot data on 28 subjects.^45^ No difference in PDI was expected between face-to-face and eHealth self-management and the region of non-inferiority was defined as a difference of five PDI points. The sample size was calculated to have at least 80% power to show non-inferiority based on a one-sided test with alpha equal to 0.025 (hence, equivalent to a two-sided test with alpha=0.05). A simulation study with 2000 simulations was used, and the power was defined as the percentage of sampled datasets where non-inferiority has been shown using the ANCOVA approach. With 79 subjects in the eHealth and the face-to-face group, there is at least 80% power to show non-inferiority.

To show superiority of eHealth intervention vs usual care based on a two-sided (ANCOVA) test with alpha equal to 0.05, 83 subjects per group are required to detect with at least 80% power a difference of 5 points. Note that having at least 80% power for each of the two comparisons separately does not guarantee 80% power simultaneously.

Strictly speaking, fewer patients are required in the face-to-face group compared with the two other groups. However, given the small difference (79 vs 83), it was decided to recruit an equal number of patients in each of the three groups.

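### The principal investigator can open the allocation file although an independent member already allocates: an avoidable concealment risk, with a minor query on the block sizes

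*Protocol article*

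**What the plan says.** All the randomisation details are in the protocol article under Allocation and randomisation.

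- The sequence comes from a script written by a group member who has no part in recruitment, intervention or analysis.
- "The script’s output will be transferred to a structured Excel file, which facilitates the allocation of each participant to their respective treatment arm", within four strata defined by recruitment setting.
- "Access to and utilisation of this Excel file will be restricted to the principal investigator and an independent member of the research group". The independent member's only tasks are to allocate new participants and give them identifiers.
- The method is "randomly permuted blocks with random block sizes (3–6"). The Sample size section plans equal groups: "it was decided to recruit an equal number of patients in each of the three groups".

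Under Participant screening, recruitment and consent, "an initial screening is conducted by a member of the research team", with no further detail on who that is. The same section says: "Participants are not blind to the intervention nor the different arms".

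**The concern.** Two of the three people who touch the sequence are deliberately kept apart from the rest of the trial. The third, the principal investigator, is not, and the article gives no reason why that role needs the file during recruitment.

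Anyone who can see the next assignment in a stratum and can also influence who enters, or when, can steer patients towards or away from an arm. There is room for this here. The Eligibility criteria exclude people judged mentally or physically unfit to take part or unable to stay for the full study, and a second telephone consultation may precede consent. Selection of this kind would reach the primary analysis. The model under Data analysis sets the true baseline means equal across arms on the strength of randomisation, and it adjusts for observed baseline differences in the Pain Disability Index (PDI). It cannot adjust for prognosis that was not measured. Blinding the analysis centre does not help, because the selection happens before any data exist.

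The block sizes raise a separate and smaller matter. A block can hold three arms equally only if its size is a multiple of three, and the stated range, read literally, contains sizes that are not.

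**Working it through.** **Access to the list.** No arithmetic applies, so the roles are set side by side.

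| Role | Access to the sequence | Stated separation from the trial |
|---|---|---|
| Script author | Generates it | Outside recruitment, intervention and analysis |
| Independent member | Opens and uses the file | Allocation and identifiers only |
| Principal investigator | Opens and uses the file | None stated |
| Screening team member | None stated | None needed if the list is concealed |

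The file receives the script's output and is used to allocate by stratum. The natural reading is that it holds assignments not yet used. That is an inference, since the article says neither that unused rows are visible nor that they are hidden.

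**Block sizes: divisibility.** 3/3 = 1 and 6/3 = 2 are whole numbers; 4/3 = 1.33 and 5/3 = 1.67 are not. Only 3 and 6 in the range give 1:1:1 within a block.

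**Block sizes: the plan's own sample size first.** Inputs from the Sample size section are SD 15, baseline correlation 0.65, difference 5, two-sided alpha 0.05, power 80% and dropout 7%.

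- Residual SD = 15 × √(1 − 0.65²) = 11.40.
- The normal approximation, n = 2 × (1.960 + 0.842)² × 11.40² / 5², gives 82 per group after rounding up.
- With the noncentral t distribution, power is 79.7% at 82 and 80.2% at 83, so the stated 83 is reproduced.
- 83 / 0.93 = 89.2, rounded up to 90 per group and 270 in total, as stated.

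**Block sizes: effect on balance.** Stratified permuted blocks were simulated in 1,500 trials of 270 patients. The article gives no stratum sizes, so three splits were assumed: 90/90/45/45, 68/68/67/67 and 120/100/30/20. Sizes were drawn with equal probability. In blocks of 4 and 5 the surplus places went to randomly chosen different arms.

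| Sizes drawn | Mean difference, largest minus smallest arm | 95th percentile | 95th percentile within a stratum |
|---|---|---|---|
| 3 and 6 | 1.3–2.1 | 3–4 | 2 |
| 3, 4, 5 and 6 | 5.5–5.7 | 11 | 5–6 |

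**Block sizes: effect on power.** Superiority power = Φ(5 / (11.40 × √(1/a + 1/b)) − 1.96), with 166 evaluable patients in the two arms:

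- 83 and 83: 80.7%
- 78 and 88 (difference 10): 80.5%
- 76 and 90 (difference 14): 80.4%

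The loss is 0.3 points or less.

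**Block sizes: effect on predictability.** In a stratum of 67, consider someone who sees all earlier assignments and always guesses the arm with fewest patients so far. That person is right about 57% of the time with sizes 3 and 6, and about 45% with 3, 4, 5 and 6. Chance is 33%. The odd sizes make the sequence harder to guess.

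**The case against.** The best defence is that the harm is argued from silence. Nothing in the article says that the principal investigator screens, consents or enrols. Allocation belongs to an independent person, and a condensed article may leave the delegation of tasks and the masking of the file to the full protocol. This stands in part. It rules out calling the arrangement a breach. It does not remove the point, because the access is stated as a rule and not left unsaid, and no safeguard is set beside it.

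A reader might infer that the principal investigator knows every coming assignment. The article does not say so, as it does not describe what either user sees of the unused rows.

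A reader might also infer that the block range weakens concealment, or that a fixed share of assignments becomes certain once the earlier ones in a block are known. Neither is supported. Literal sizes 4 and 5 lower predictability, and such shares assume known, fixed block sizes whereas the plan draws them at random. They also require knowledge of the running allocations in the stratum, which the article does not give to recruiters.

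On balance, 3–6 may simply be shorthand for 3 and 6. In that case nothing is wrong except the wording.

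**Conclusion.** The point holds as a weakness in allocation concealment that is easily removed. A role not placed outside recruitment may open and use the allocation file, while the person who needs it is already independent. The size of any resulting bias cannot be calculated from the article, and none is shown to have occurred. The conclusion rests on reading the file as containing unused assignments, and on the article being silent about the principal investigator's part in screening and enrolment. If the full protocol excludes that role from both, or masks unused rows, one sentence would settle the matter.

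The block-size wording is a secondary clarification. Its possible cost is a slightly larger arm imbalance and practically no power, under the assumed stratum sizes and the assumed handling of surplus places.

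**What to change.** **Access.** For the remaining recruitment, expected to run until January 2028, withdraw the principal investigator's access to unused assignments until recruitment closes. Only the independent member should hold the list and release one assignment at a time, after eligibility and consent are recorded, with a time-stamped log. The cost is a change of file permission, a sentence in the protocol and a named independent deputy to cover absence.

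This fits the order in Table 1, where consent precedes allocation. Holding each assignment back until baseline is recorded would be a different change, because Table 1 places the baseline assessment after allocation. It should not be added unless that order is deliberately revised.

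**Block sizes.** State the sizes as 3 and 6 if that is what is meant, and check whether the script can draw 4 or 5. Enrolment began on 26 May 2024, so a sequence is already in use. If 4 and 5 have been drawn, describe this accurately. Before regenerating any unused part, weigh the small gain in balance against the greater predictability of sizes 3 and 6.
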